## Abstract

**Background:**

HIV clinical guidelines recommend hypertension detection and management to lower cardiovascular disease risk, but these have not been effectively implemented for people living with HIV (PWH). Addressing this implementation gap requires community-engaged implementation studies focused on addressing implementation barriers specific to the HIV care context.

**Methods:**

This protocol describes a type 2 effectiveness-implementation hybrid study conducted in nine primary care clinics in Johannesburg. The study will evaluate the effect of implementation strategies on guideline-recommended blood pressure assessment and management in HIV clinics and the effects of assessment/management on patient blood pressure. A stepped-wedge, cluster randomized study design was used to randomize clinics to the time at which they receive the implementation strategies and patient intervention. The implementation strategies tested include identifying and preparing care champions, changing record systems, conducting ongoing training, providing audit and feedback, and changing the physical structure/equipment. The patient intervention tested includes detection of elevated blood pressure, educational materials, lifestyle modification advice, and medication where needed. Implementation outcomes include adoption, fidelity (co-primary outcome), cost, and maintenance of the blood pressure assessment protocol in participating clinics, while patient outcomes include reach, effectiveness (co-primary outcome), and long-term effects of the intervention on patient blood pressure. These will be assessed via direct observation, study records, staff logs, medical chart reviews, and patient and healthcare worker surveys. To examine effects on the implementation (intervention fidelity) and effectiveness (patient blood pressure changes) co-primary outcomes, we will use the standard Hussey and Hughes model for analysis of stepped-wedge designs which includes fixed effects for both interventions and time periods, and a random effect for sites. Finally, we will examine the costs for the implementation strategies, healthcare worker time, and patient-facing intervention materials, as well as the cost-effectiveness and cost-utility of the intervention using study records, patient surveys, and a time and motion assessment.

**Discussion:**

This study will address knowledge gaps around implementation of cardiovascular disease preventive practices in HIV care in South Africa. In doing so, it will provide a dual opportunity to promote evidence-based care in the South African HIV care context and help refine implementation research methods to better serve HIV populations globally.

**Trial registration:**

ClinicalTrials.gov: NCT05846503. Registered on May 6, 2023. https://classic.clinicaltrials.gov/ct2/show/NCT05846503.

**Supplementary Information:**

The online version contains supplementary material available at 10.1186/s43058-024-00640-6.

Contributions to the literature
This protocol describes the evaluation of context-specific implementation strategies to improve the detection and management of hypertension in HIV care settings in Johannesburg, South Africa.Implementation strategies identified through community-engaged formative work are used to promote guideline-recommended hypertension detection and management in routine HIV care.The evaluation employs robust implementation research methods that can produce internally and externally valid findings to inform integration of guideline-recommended hypertension care practices into routine HIV care.

## Background

Widespread availability of antiretroviral therapy has extended survival among people with HIV (PWH) such that age-related chronic conditions are growing in prevalence for this population [1–5]. Notably, the cardiovascular disease (CVD) burden for PWH has tripled over the past two decades, accounting for 2.6 million disability-adjusted life-years lost each year globally [6]. South Africa has become an epicenter of the dual burdens of infectious and non-communicable diseases, with the highest absolute number of PWH worldwide [7] and growing burdens of CVD [8–10]. Addressing the dual burden of HIV infection and CVD risk factors faced by PWH in South Africa requires integrated care models that account for financial and human resources limitations present in the healthcare system [11].

Evidence-based recommendations endorse hypertension detection and management to lower CVD risk in PWH [12], but these have not been effectively implemented for this population [13–15]. Studies have shown hypertension management is suboptimal in HIV care [16, 17], and that PWH are less likely to receive guideline-recommended CVD preventive care than those without HIV [18]. Identified challenges to implementing evidence-based hypertension management include lack of investments for integrating HIV and CVD care, lack of standardized screening practices, and lack of validated care algorithms [19, 20]. In addition, the PEPFAR and Global Fund strategies have often led to vertically siloed HIV care models wherein other health conditions are addressed in separate settings. Overcoming these challenges requires community-engaged implementation studies focused on addressing barriers to guideline implementation specific to HIV care settings.

Based on our community-engaged formative work [21], we designed context-specific implementation strategies to improve hypertension detection, treatment, and control among PWH in South Africa. Here, we describe the protocol of a type 2 effectiveness-implementation hybrid study aimed at evaluating the effects of our implementation strategies and clinical intervention in nine primary health care clinics in the city of Johannesburg, South Africa. To inform decision-makers of the potential costs associated with integrating hypertension detection and control in HIV care, we also describe the protocol for evaluating budget impact and cost-effectiveness of this multi-strategy approach.

## Methods

### Setting

The study is being conducted in public sector primary care clinics that provide HIV care in Region F of Johannesburg, South Africa. The region has 14 primary care clinics that serve about 700,000 residents by offering reproductive and sexual health care, mobile and community outreach services, HIV screening and treatment, and tuberculosis screening and treatment. Prior to this study, two clinics also had hypertension management programs in place. A mix of patients with and without HIV are seen in these clinics, and a high proportion of patients are non-native migrants (> 75%). Primary care services are led by nurses, while HIV diagnosis and treatment services are led by nurses trained in the Nurse Initiation and Management of Antiretroviral Therapy protocol. All 14 primary care clinics were invited to participate in the study: four declined (due to renovations, limited staff, or unsuitable patient care flow), and one clinic was selected for a pilot study. The remaining nine clinics agreed to participate and were enrolled in the study.

### Study design

 We employ a type 2 effectiveness-implementation hybrid study type to simultaneously test implementation strategies and a clinical intervention [22]. Specifically, we will evaluate the effect of the implementation strategies on guideline-concordant hypertension care practices in participating clinics, as well as the effects of the guideline-concordant care on patient blood pressure. For the evaluation, we employ a stepped-wedge, cluster randomized trial design. This protocol aligns with the Standards for Reporting Implementation Studies Statement [23] and with the CONSORT statement for reporting stepped-wedge, cluster randomized trials [24]. The study protocol is registered in ClinicalTrials.gov (NCT05846503).

We selected a stepped-wedge, cluster randomized trial design for three reasons. First, since the study has the potential to improve healthcare delivery, all participating clinics wanted to receive the intervention and this design ensures all clinics do. Second, this is an implementation study testing interventions under routine care conditions; as such, a sequential roll out of the proposed intervention allowed us to alter care for a proportion of clinics at a time. Finally, given the research and clinical resources available, rolling out the intervention in all clinics at the same time (i.e., cluster RCT) was not feasible; thus, a sequenced rolled out was preferred. These reasons outweighed the main limitations of the clustered randomized stepped wedge study design – selection bias and confounding due to temporal changes in clinical care concurrent with the intervention rollout [25].

Table 1 depicts the trial design, periods, and sequence allocation order. In our study, clinic was the unit of randomization. Clinics were stratified into three groups based on clinic population size, categorized by monthly patient head count as small (1000 to 3499), medium (3500 to 6999), and large (7000 to 10000). Clinics were then randomized via a computer-generated sequence to cross-over from the control to the intervention condition starting in Period 2 until all clinics crossed over to intervention. One clinic from each size stratum was randomly selected for each sequence. The study biostatistician ([name]) generated the randomization schedule and assigned clusters to sequences using SAS software, version 9.4 (SAS Institute Inc, NC USA). [name] enrolled the clusters.

The allocation sequence began with an observation period where none of the clinics had neither received the implementation strategies nor rolled out the patient intervention (Period 1). In this period, we collected implementation and clinical data under the control condition. After the control period, clinics crossed-over to the intervention condition, three at a time based on their randomization sequence. To date, all nine clinics have-crossed over to the active intervention period which will run from study months 4–15 (Periods 2–5). Since this intervention was randomized at the clinic level and involves providing clinical care, blinding was not possible. For each step, clinics were notified one month in advance prior to initiation of the intervention.

At month 14, all clinics will initiate a two-month offboarding transition period (Period 5). Here, research staff will support clinic staff to ensure that implementation strategies continue to be executed, while also helping them to further integrate the blood pressure assessment protocol within routine care. From months 16–27, research staff will be withdrawn from clinics and a maintenance observation period will begin (see Table 1).

**Table 1 Tab1:**
[figure not shown]
Trial design and random sequence allocation order

### Study populations

 The study includes two analytic study populations: the implementation evaluation and the effectiveness evaluation population. Figure 1 shows the implementation and effectiveness population selection flow. The implementation evaluation population will include all patients ≥ 18 years old who present to clinic for care and are seen in the study triage room where vital signs are taken. Data from this population will be collected by a research staff member situated in the triage room who will record whether blood pressure is measured, the blood pressure values obtained, and whether educational materials are delivered at each visit. These data will be recorded using a REDCAP form developed for the study. These patients will contribute data to the primary implementation outcome for all study steps, including control and intervention periods.

The effectiveness evaluation population will include patients aged ≥18 years old with elevated blood pressure (defined as systolic blood pressure ≥140 mmHg or diastolic blood pressure ≥90 mmHg), at any point during the active intervention period, and with a known diagnosis of HIV (determined by self-report or medical chart review). Patients are eligible regardless of their prior history of hypertension or use of blood pressure lowering medications. Research staff situated in the triage vitals room will recruit these patients and obtain consent to prospectively abstract demographic and clinical data from their medical charts. Patients will be included in the study through continuous recruitment. Patients with HIV and elevated blood pressure then become part of the effectiveness outcome population from the date of their first elevated blood pressure value is recorded and will remain under observation for all additional study visits.

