**EFFECTIVENESS EVALUATION**		
**Outcome definitions**	**Time points**	**Data source**
***Reach*** Percentage and representativeness of patients with elevated blood pressure and HIV that receive the intervention	At the initial / enrollment study visit (months 1–15)	• Study REDCAP form • Medical charts
***Effectiveness*** Primary clinical outcome: difference in mean systolic BP between the intervention and control periods	All visits in months 1–15, excluding the two months following intervention initiation	• Medical charts
***Cost-effectiveness*** Health utility of the intervention and direct medical costs of additional patient visits and/or hospitalizations	Control, active intervention (months 1–15), and maintenance periods (months 16–27)	• Quality of life (EQ-5D) patient questionnaire • Patient-reported cost survey • Study records
***Patient-level Maintenance*** Extent to which blood pressure improvements observed during the intervention phase are maintained	Active intervention (months 4–15) and maintenance (months 16–27) periods	• Medical charts • Study REDCAP form

*BP* blood pressure

*Adoption* will be determined as the percentage and representativeness of clinics that complete the blood pressure assessment protocol at the initial study step (i.e., did they roll out intervention? Yes/No). Intervention fidelity (*primary implementation outcome*) will be defined as the difference in percentage of patient visits with recorded blood pressure measurement between intervention and control periods. We will also keep track of adaptations made to the blood pressure assessment protocol via care coordinator notes and reports. Clinic-level *maintenance* of the intervention will be defined as the extent to which blood pressure continues to be assessed after the active intervention period ends based on medical chart reviews. We will also assess the normalization of the blood pressure assessment protocol using a 23-item questionnaire [32] healthcare workers will complete at the beginning and at the end of the maintenance period.

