*Reach* will be defined as the percentage and representativeness of patients with elevated blood pressure that receive educational materials and lifestyle modification advice / medication, among all patients with elevated blood pressure. Changes in patient blood pressure (*primary effectiveness outcome*) will be defined as the difference in mean systolic blood pressure between the intervention and control periods. Patient-level m*aintenance* of intervention effects will be defined as the extent to which blood pressure improvements observed during the active intervention period are sustained during the maintenance period.

The *cost* evaluation will examine direct medical costs for intervention delivery, including implementation strategies, patient-facing intervention materials, additional staff time required to deliver the intervention, and additional blood pressure medication. One-time costs for implementation strategies will be estimated from the study records. The additional time burden associated with integrating the blood pressure assessment protocol in participating clinics will be assessed using a time and motion assessment in a random sub-sample of 100 patients at each clinic during control, active intervention, and maintenance periods (900 per period; total *n* = 2,700). This assessment will collect data on the start and end time of different procedures during a patient’s journey through a routine clinic visit. Finally, this patient subsample will also complete a survey regarding medical expenditures for outpatient and inpatient care utilization during the last 12 months, and the EQ-5D quality of life questionnaire [33] to determine health utility.

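### The entry rule for the effectiveness population starts at month 4, but the co-primary blood pressure contrast, its data window and the sample size need control patients from month 1

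*Protocol article*

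**What the plan says.** Study populations requires elevated pressure "at any point during the active intervention period, and with a known diagnosis of HIV". Study design gives the dates: "active intervention period which will run from study months 4–15 (Periods 2–5". Patients count "from the date of their first elevated blood pressure value is recorded and will remain under observation for all additional study visits", and research staff "obtain consent to prospectively abstract demographic and clinical data from their medical charts".

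The preceding paragraph of Study populations treats the implementation population differently: "These patients will contribute data to the primary implementation outcome for all study steps, including control and intervention periods". No such sentence follows for the effectiveness population.

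Other sections assume control patients from the start. Outcome measures and definitions sets the co-primary effectiveness outcome as the "difference in mean systolic blood pressure between the intervention and control periods". Table 3 gives its data window as "All visits in months 1–15, excluding the two months following intervention initiation", and dates the Reach enrolment visit to months 1–15. Effectiveness outcomes analyses repeats the months 1–15 window and classifies each reading by the clinic's status when it was taken. Of Period 1, Study design says: "In this period, we collected implementation and clinical data under the control condition". The sample size section powers the trial on a 5 mmHg difference between intervention and control periods, with three steps and nine clinics over 15 months.

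**The concern.** In a stepped-wedge trial, Period 1 is the only time when every clinic is under control, and the only control time that the first sequence has. An entry rule that opens in month 4 leaves out patients whose elevated reading falls only in months 1–3. Because abstraction is prospective, the text gives no clear route back to Period 1 data even for patients who qualify later. The eligibility rule therefore conflicts with one of the two co-primary outcomes.

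The timing adds weight. Study design reports that all nine clinics have crossed over, so control data can no longer be newly collected. If the rule stays ambiguous until analysis, the control group could be settled after the blood pressure results are known.

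**Working it through.** **Inputs.** Nine clinics, three crossing at a time, from Period 2 (Study design). SD 20 mmHg, difference 5 mmHg, intra-class correlation (ICC) 0.01, 506 patients before and 1,640 after a design effect of 3.2, 46 per clinic per step, 184 per clinic annually (Sample size calculation). Two-sided alpha of 0.05 is assumed. Table 1 is not shown, so I assume crossovers in Periods 2, 3 and 4 with equal cells.

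**1. The plan's total.**
- 506 × 3.2 = 1,619, close to 1,640 (1,640 / 506 = 3.24, so the design effect was rounded).
- Three periods: 46 × 9 × 3 = 1,242, too few.
- Four periods: 46 × 9 × 4 = 1,656, which fits; 1,640 / 36 = 45.6, rounded to 46, and 184 = 46 × 4.

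With three steps over 15 months, the fourth period is the Period 1 baseline. Counting Periods 2–5 would also give four, but they span 12 months, not the 15 assumed. (Separately, 506 matches 80% rather than 85% power. That does not affect this count.)

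**2. Control time inside the entry window, by calendar month.**
- Control clinic-periods: 9 (Period 1) + 6 (Period 2) + 3 (Period 3) = 18.
- Without Period 1: 9 of 18 remain, or 9 × 46 = 414 of 18 × 46 = 828 planned control patients.
- The first-sequence clinics have no control time left.

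In clinic-months, with crossover months c, control time is 3 × Σ(c − 1) in total and 3 × Σ(c − 4) from month 4:

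| Assumed crossover months | Total | From month 4 | Share left |
|---|---|---|---|
| 4, 6, 8 | 45 | 18 | 40% |
| 4, 7, 10 | 54 | 27 | 50% |
| 4, 8, 12 | 63 | 36 | 57% |

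**3. Precision under the Hussey and Hughes model.** With I clinics, T periods, cell-mean variance s² = (1 − ICC) × 400 / 46 and clinic variance τ² = ICC × 400:

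Var = I s² (s² + Tτ²) / [(IU − W) s² + (U² + ITU − TW − IV) τ²]

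U is the number of intervention cells (18). W sums the squared period totals (9 + 36 + 81 = 126). V sums the squared clinic totals (3 × (9 + 4 + 1) = 42). At ICC 0.01, s² = 8.609 and τ² = 4.
- Period 1 included (T = 4): Var = 9 × 8.609 × 24.609 / (36 × 8.609 + 90 × 4) = 2.846, SE 1.69. Power = Φ(5/1.687 − 1.96) = 84.2%.
- Period 1 absent (T = 3): Var = 9 × 8.609 × 20.609 / (36 × 8.609 + 54 × 4) = 3.036, SE 1.74. Power = Φ(5/1.742 − 1.96) = 81.8%.

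| ICC | Power with Period 1 | Power without |
|---|---|---|
| 0.005 | 86.8% | 85.8% |
| 0.01 | 84.2% | 81.8% |
| 0.05 | 80.7% | 74.0% |

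These figures do not remove the two excluded months after each crossover, and they do not model repeated measurements.

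**4. The per-clinic reading.** If the period meant each clinic's own time after crossover, every retained cell would be an intervention cell. The treatment column would then equal the sum of the period columns, and the effect could not be estimated.

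**The case against.** The strongest reply is that one loose phrase is set against the rest of a condensed article. Clinical data were collected in Period 1, Reach enrolment starts in month 1, the sample size compares control with intervention, and the analysis uses months 1–15. The intention is probably enrolment from month 1, and Fig. 1 or the full protocol may say so. That stands as to intention, but nothing shown lifts the restriction in Study populations.

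A reader might infer that the control side is empty. The text does not support that as the main reading. Study design, Table 3 and the maintenance analysis all date the active period or phase to months 4–15, and clinics still waiting to cross remain under control in those months. Only the remark that clinics crossed over to the active period leans the other way.

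Nor is it settled that Period 1 contributes nobody. A patient elevated in Period 1 and again in month 5 meets the criterion, and observation is dated from the first elevated value. Prospective abstraction leaves the use of such readings uncertain. The loss computed above is therefore the full-loss case.

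A reader might also infer that earlier readings of later-qualifying patients must be non-elevated, so that the control mean would be too low. That does not follow, because an elevated reading outside the entry window does not trigger entry. Such readings would select the control side on a later value, with a bias of undetermined direction.

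**Conclusion.** The contradiction is real and should be resolved before analysis, because a co-primary outcome depends on it. On the better-supported calendar reading, patients elevated only in Period 1 are excluded. That period is about half of the control clinic-periods (40–57% of control clinic-months would remain under the schedules tried) and all control time of the first-sequence clinics. The contrast remains estimable. The loss of power is modest at the protocol's ICC, about 2 points, and about 7 points at ICC 0.05. The larger cost is that three of nine clinics lose their within-clinic comparison. Non-estimability arises only on the less supported per-clinic reading.

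The figures rest on equal cells of 46 and crossovers in Periods 2 to 4. The documents do not show that control patients were in fact left unenrolled, and this point does not claim it.

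**What to change.** Restate the criterion as elevated blood pressure at any visit in months 1–15, with the clinic in either the control or the intervention condition, and with the same identification and consent process in both. Make Study design, Study populations, Table 3, Sample size calculation and Effectiveness outcomes analyses agree with it.

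- **If control-period patients were already enrolled**, as Study design and Table 3 suggest, this corrects the text and costs a sentence.
- **If they were not**, state that the control side is limited to Period 2 onward, and restate sample size and power on that basis. Recruitment under control cannot be repeated. Any retrospective identification from triage records would need consent and separate confirmation of HIV status, which is not among the items that Study populations lists for the triage form. It would also need chart abstraction.

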#### Effectiveness outcomes analyses

To assess *reach*, we will summarize participant-level indicators, including age, sex, blood pressure at enrolment, treatment for blood pressure at enrolment, and HIV history by clinic at the initial intervention visit. We will then estimate the percentage of patients with elevated blood pressure that receive the initial educational materials and lifestyle advice plus medication (numerator), from all patients identified with elevated blood pressure (denominator). Demographic and clinical characteristics between reached/not reached patients will be compared using chi-square / Fisher’s exact tests for categorical variables, and independent samples t-tests / Wilcoxon rank-sum tests for continuous variables.

To assess clinical impact of the intervention (*primary effectiveness outcome)*, we will examine differences in mean systolic blood pressure between intervention versus control clinics. We will estimate the effect of clinic-level intervention exposure (no intervention versus intervention by research staff) using mixed effects linear regression models. In addition to the standard stepped-wedge model outlined previously, we will include a random effect to account for correlation due to repeated measurements on participants. We will also include randomization strata, sociodemographic characteristics (age, sex, and immigration status), and clinical characteristics (prior treatment for hypertension, HIV regimen, CD4 count, and viral load) in our final multivariable model to obtain an adjusted estimate of the intervention effect.

The effectiveness analysis will use data from months 1–15 while censoring data from the first two months of intervention initiation (i.e., the transition period from control to intervention; see Table 1). This is to provide time for the intervention to impact patient behavior and medication initiation, thus giving time for blood pressure to be affected. We will follow an intention-to-treat approach in which data from individual patients will be analyzed according to the clinic intervention status at the time of measurement. Standard model diagnostic procedures will be used to evaluate model fit, and transformations will be applied (e.g., log transformation) as needed.

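### The reading that qualifies a patient also counts as outcome data, unevenly across conditions, so regression to the mean can look like a modest treatment benefit

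*Protocol article*

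**What the plan says.** All references are to the protocol article.

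- **Entry.** Under Study populations, the effectiveness population consists of adults with HIV and elevated blood pressure, "defined as systolic blood pressure ≥140 mmHg or diastolic blood pressure ≥90 mmHg", occurring "at any point during the active intervention period". Entry is open-ended: "Patients will be included in the study through continuous recruitment".
- **Start of observation.** Patients "become part of the effectiveness outcome population from the date of their first elevated blood pressure value is recorded" and stay under observation for later visits.
- **Outcome.** Under Outcome measures and definitions, the primary effectiveness outcome is "defined as the difference in mean systolic blood pressure between the intervention and control periods".
- **Visits counted.** Table 3 (effectiveness row) gives "All visits in months 1–15, excluding the two months following intervention initiation".
- **Exclusion and classification.** Effectiveness outcomes analyses describes "censoring data from the first two months of intervention initiation" and states that "data from individual patients will be analyzed according to the clinic intervention status at the time of measurement".
- **Model.** The plan is a Hussey and Hughes model with fixed period effects and a random site effect, plus a patient random effect. The adjusted model adds randomization strata and sociodemographic and clinical covariates, including prior hypertension treatment. Blood pressure at enrolment is listed as a descriptor for reach, but not as a covariate for the primary outcome.

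Nowhere does the article set the qualifying reading aside as a baseline. Only an exploratory cohort analysis requires two or more visits, so the primary analysis keeps patients whose sole reading is the one that selected them.

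**The concern.** A reading chosen because it is high is, on average, higher than the same patient's next reading, treated or not. This does no harm if qualifying readings make up the same share of the data in both conditions. Three features of the plan push the shares apart:

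1. Control time comes first in a stepped wedge. Many patients enter under control and supply their follow-up readings under intervention.
2. Blood pressure is probably measured less often under control. The Implementation strategies section says the clinics lacked equipment, and raising measurement is the other co-primary hypothesis. Fewer control measurements mean fewer control follow-up readings for each entry reading.
3. The two-month exclusion follows clinic crossover. It removes readings, including qualifying ones, from the intervention side only. No matching window is removed under control or after a patient's own entry.

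At stake is the primary effectiveness estimate. Success on the fidelity outcome could generate part of an apparent blood pressure effect. That part would carry into the cost per mmHg, and the maintenance analysis uses the same model.

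**Working it through.** The article gives no figure for this bias, so there is none to reproduce. From the Sample size calculation section come the 5 mmHg target and the SD of 20 mmHg; the threshold of 140 comes from Study populations. Everything else is assumed.

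**Step 1: expected fall on repeat, no treatment.** For entry on systolic pressure alone, with a = (140 − μ)/20 and λ = φ(a)/(1 − Φ(a)):

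- mean qualifying reading = μ + 20λ
- expected fall at the next reading = 20(1 − ρ)λ

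| μ (assumed) | ρ (assumed) | a | λ | Qualifying mean | Fall |
|---|---|---|---|---|---|
| 125 | 0.5 | 0.75 | 1.329 | 151.6 | 13.3 |
| 130 | 0.6 | 0.50 | 1.141 | 152.8 | 9.1 |
| 130 | 0.8 | 0.50 | 1.141 | 152.8 | 4.6 |
| 135 | 0.8 | 0.25 | 0.964 | 154.3 | 3.9 |

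The fall, 3.9 to 13.3 mmHg, is of the same order as the target or larger. This is not yet the bias, which depends on how unequal the shares of qualifying readings are and on what the model absorbs.

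**Step 2: null simulations.** Nine clinics, three crossing at each of months 4, 7 and 10 (assumed, because Table 1 is not shown), with no treatment effect. Entry is at the first elevated measured reading, and outcomes run from that reading onward. Entries are the intervention-minus-control estimate in mmHg with the two-month exclusion applied, by percentage of control visits at which blood pressure is measured.

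| Model and inputs | 20% | 40% | 70% | 90% |
|---|---|---|---|---|
| A. Clinic and period effects, no patient effect; entry on systolic only | −2.8 | −1.8 | −0.9 | not run |
| B. As A, with patient random effect and entry also on diastolic ≥90 | not run | −1.4 | −0.45 | −0.2 |
| C. Separate run: period effects, patient random effect, both entry routes | −1.4 | −0.9 | −0.4 | −0.3 |

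A assumes systolic mean 128, between-person SD 14, within-person SD 12, visits about every 2 months, and 95% measurement under intervention. B also assumes diastolic mean 80 and a moderate systolic–diastolic correlation. The Monte Carlo standard error is 0.1–0.3 for A and 0.1–0.2 for B. With monthly time effects, the B figures become −0.9, +0.1 and +0.2.

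A wider grid (D) used mean 130, correlation 0.6 or 0.8, visits every 1–3 months, and control measurement of 20–90% against 90% under intervention, with a patient random effect and five periods. It gave about +0.3 to −4.8. Qualifying readings made up 21–93% of control data and 2–34% of intervention data.

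**Step 3: what drives it.** One case from D (visits about every 2 months, 40% against 90%):

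- no exclusion: −0.5
- with the exclusion: −1.4
- with the exclusion and the qualifying reading dropped: −0.2

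Across D the exclusion typically adds about 0.2 to 2 mmHg of false benefit. With the qualifying reading dropped, the estimate lies between −0.7 and +0.8 in D and about −0.2 to −0.5 in C.

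**Step 4: against the target.** 1/5 = 20%, 2/5 = 40% and 4.8/5 = 96% of the 5 mmHg difference.

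**The case against.** The strongest reply is that the planned model handles most of this and that the rest hangs on numbers the article does not give. Both parts largely stand. Control measurement rates, visit spacing, the variance split and crossover months are all assumed. If measurement is equal in both conditions and recruitment starts everywhere in month 1, the bias is about zero. The covariate-adjusted model, with prior hypertension treatment in it, has not been simulated.

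An unseen analysis plan could also treat the entry reading as baseline, and observation from a date does not say outright that the reading on that date is an outcome value. That tempers confidence. Still, the article counts all visits and sets none aside, so its rules followed as written include the reading.

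Four stronger conclusions are tempting but unsupported:

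- **That the bias is as large as the raw difference.** Crude null differences of −4.4 to −10.2 mmHg do appear in the simulations (−7.6 in A at 40%), but the planned estimator has fixed period effects.
- **That the exclusion strips qualifying readings from the intervention side.** It removes only those in a clinic's first two months. With continuous recruitment, later ones stay in.
- **That control data are mostly qualifying readings.** This is a simulation result, not a fact in the document. In B the share was about 45% at 70% measurement and 38% at 90%.
- **That patients already treated for hypertension offer a clean comparison.** They too enter only through a measured elevated reading and face the same selection.

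**Conclusion.** The concern holds as a conditional bias of modest size. The rules as written put a selected reading into the primary outcome, with a larger share on the control side, and the one-sided exclusion adds to the imbalance. Where control measurement is clearly lower, the direction favours the intervention. In A to C, under no true effect, the remaining bias is near zero at similar measurement rates and roughly −1 to −2 mmHg at 20–40% control measurement (−2.8 at 20% in A, which omits the planned patient effect). The worst case in D, −4.8 mmHg, nearly equals the target, but it is an extreme of assumed inputs and not an expectation.

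A related defect lies in the text itself. Elevation must occur in the active intervention period, which Study design dates to months 4–15, yet Table 3, the outcome definition and the analysis section use control readings from month 1. Read clinic by clinic, the entry rule leaves no control readings at all. Read study-wide, Period 1 supplies no entrants; the bias then remains, at about −2.2 mmHg with 40% control measurement and −1.0 with 70% under the inputs of B.

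**What to change.** In both conditions, define the qualifying reading as baseline, leave it out of the primary outcome, analyse only later readings, and enter the qualifying systolic value as a covariate. Keep the all-readings analysis as a sensitivity analysis, so the effect of the change is visible. State in Study populations, Table 3 and the effectiveness analysis section when the elevated reading may occur, and reconcile that with the use of control readings from month 1.

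The change is to wording only and needs no new data. The cost is that patients with a single reading drop out and some precision is lost. Those patients carry no blood pressure information after entry.
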